6.1.2 On-Study Evaluations

Study visits must be scheduled on the weeks indicated in the schedule of events with a window period of:

- 7 days on each side of target date (first year of study)
- 14 days on each side of target date (all subsequent visits)

6.1.3 Evaluations for subjects randomized to HAART who do not start study treatment.

Subjects who do not initiate study treatment within 24 hours of randomization will be reevaluated at week 1 to determine the circumstances that have led to this delay in beginning their therapy.

6.1.4 Evaluations for subjects not randomized to HAART who initiate or re-initiate study treatment

for clinical or immunologic reasons.

Subjects will be seen two weeks after initiation of therapy, and monthly until HIVRNA <50 copies/mL. After this they will follow their original visit schedule.

6.1.5 Treatment Discontinuation Evaluations

Subjects who permanently discontinue study treatment prior to completion of the one year treatment period will have all Month 12 evaluations performed as soon as possible, and then continue to be followed per the schedule of visits.

6.1.6 Post-Treatment Evaluations

Patients who will have been randomized to receive treatment in the first year of the study will continue to be followed on a quarterly basis off treatment for an additional period of two years. All untreated patients will be followed within the study protocol for a period of three years, the same duration as the treated patients.

6.1.7 Off-Study Evaluations

All participants who discontinue the study early will be contacted by telephone one month after termination. In addition, those who were receiving medication at the time of early discontinuation will be contacted again 2 months post-termination.

6.1.8 Pregnancy

### Women of childbearing potential must have a negative serum pregnancy test (β-HCG) at screening and a negative urine or serum pregnancy on the day of initiation of HAART. If a woman becomes pregnant while on study, she must be informed of her options. She will also be informed of the lack of safety data regarding the use of certain antiretroviral drugs in pregnancy. Changes of drugs within a given class or across classes will be permitted in order to maintain HAART that is safe during pregnancy. Conception after initiation of treatment will not constitute a criterion for exclusion from the study.

### 6.2 Special Instructions and Definitions of Evaluations

6.2.1 Medical History

A medical history must be present in source documents. All diagnoses should be recorded on the case report forms according to the current Adult ACTG criteria for clinical events and other diagnoses.

Any allergies to any medications and their formulations must be documented.

6.2.2 Medication History

A medication history must be present in source documents*.* All prescription and nonprescription medications as well as alternative therapies and dietary supplements taken within 30 days of entry or since the last clinic visit, as applicable, will be noted. This will include actual or estimated start and stop dates.

6.2.3 HAART

The choice of the initial HAART regimen will be clearly indicated in the source documents and in the case report forms. All modifications to HAART including initial doses, patient-initiated and/or protocol-mandated interruptions, modifications, and permanent discontinuation of treatment will be recorded on the case report forms at each study visit*.* Subject-initiated and protocol-mandated interruptions include both inadvertent and deliberate interruptions of study drug(s) dose(s) for 7 or more consecutive days.

6.2.4 Physical Exam

Complete Physical Exam

This is required at screening, and annually thereafter. It will include height at screening, and weight at screening and then again at each subsequent time point. If at any study visit should symptoms be present which warrant a physical exam, it will be performed.

Vital Signs

Temperature, pulse, and blood pressure will be collected at all visits.

Weight

This will be recorded at each study visit.

Signs and Symptoms

Any signs or symptoms that lead to a change in treatment, regardless of grade, must be recorded on the case report forms. All signs, symptoms, and toxicities must be documented in the subject’s record, but only Grade 4 signs and symptoms must be recorded on the case report forms. All HIV related signs and symptoms, HIV-related and AIDS-defining events, deaths, and toxicities must be documented. All signs, symptoms, HIV-related and AIDS-defining events, and deaths must be recorded on the case report forms within 48 hours throughout the course of the study.

Diagnoses

All confirmed and probable diagnoses made since the last visit will be recorded in the source documentation, including current status at the time of study visit. For each diagnosis, the source document must include:

1) Date of diagnosis, date of resolution

2) Method of confirmation of diagnosis or evidence for probable diagnosis

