## 9.0 STATISTICAL CONSIDERATIONS

Any patient who is randomized will be evaluated. Parametric and distribution-free statistical methods will be used to analyze quantitative and qualitative/categorical data. Within group comparisons of baseline and follow-up measurements of plasma viral load (log-transformed) and CD4 lymphocyte counts will be conducted using Student’s paired t-test. For the principal study endpoint, a comparison of the mean log-transformed plasma viral load measures 24 months after the initial presentation in all treated vs. untreated subjects will be carried out using Student’s unpaired t-test and repeated measures analysis of variance. A similar approach will be taken to the comparison of plasma viral load measures at other time points or between sub-groups. Absolute CD4 lymphocyte counts will be treated in the same way. For issues of immunologic disease progression (defined as CD4 cell count < 350 cells/mm^3,^, and requiring a consideration of HAART), survival analytic methods (e.g. Kaplan-Meier, Cox proportional hazard regression) will be used. For other data (such as drug toxicity and treatment discontinuation), descriptive statistics will be used, with appropriate comparisons between groups as indicated.

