### 9.2 Endpoints

9.2.1 Primary Endpoints

- Comparison of the plasma viral load 24 months after initial presentation in all treated vs. untreated patients.

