9.2.2 Secondary Endpoints

- Comparison of the plasma viral load 36 months after initial presentation in all treated vs. untreated patients.
- Comparison of the CD4 lymphocyte count 24 and 36 months after initial presentation in all treated vs. untreated patients.
- Comparison of the plasma viral load 24 and 36 months after initial presentation in patients treated in the acute vs. early stage of infection.
- Comparison of the CD4 lymphocyte count 24 and 36 months after initial presentation in patients treated in the acute vs. early stage of infection.
- Toxicity of HAART in all treated patients.

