### 9.5 Monitoring

The Data Safety and Monitoring Committee of the Canadian Trials Network will serve as the DSMB for this study. The study will be reviewed every six months.

HAART associated toxicity will be assessed as follows:

- Toxicity leading to treatment discontinuation
- Evaluation of Serious Adverse Events
- Evaluation of grade 3 and 4 Adverse Events

Viral load and T-cell data in the treated versus untreated groups will be compared.

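### Deaths, AIDS-defining events and other HIV-related events are recorded in both arms, but no endpoint, analysis or monitoring item names them by randomised arm; the safety endpoint covers treated patients only

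*Protocol*

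**What the plan says.** **Collection.** Section 6.2.4 states: "All signs, symptoms, HIV-related and AIDS-defining events, and deaths must be recorded on the case report forms within 48 hours". The duty runs for the whole study and is not limited to one arm.

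**Endpoints.** The primary endpoint (9.2.1) is "Comparison of the plasma viral load 24 months after initial presentation in all treated vs. untreated patients". The secondary endpoints (9.2.2) are viral load, CD4 count and one safety item, "Toxicity of HAART in all treated patients". None names death or AIDS.

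**Time-to-event analysis.** Section 9.0 reads "For issues of immunologic disease progression (defined as CD4 cell count < 350" and says that "survival analytic methods (e.g. Kaplan-Meier, Cox proportional hazard regression) will be used". It gives no rule for censoring or for competing events.

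**Other data.** Section 9.0 adds: "For other data (such as drug toxicity and treatment discontinuation), descriptive statistics will be used, with appropriate comparisons between groups as indicated".

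**Monitoring and safety analysis.** In section 9.5 the list that includes SAEs and grade 3 and 4 events opens with "HAART associated toxicity will be assessed as follows". The only comparison between arms stated there is of viral load and T-cell data. Section 9.6 tabulates stops for toxicity, SAEs and grade 3-4 reactions, with confidence intervals, again as the toxicity of HAART.

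**Need for HAART.** Section 3.0 lists the need to start or restart HAART, in both arms, as an additional endpoint. It is not repeated in 9.2.2 or 9.6.

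**The concern.** One arm is left untreated. The other is treated for 12 months and then stopped by design. Sections 2.2.1 and the Schema say that a strategy is being tested, not a drug regimen, and section 1.3 includes the safety of that strategy among the objectives. The main clinical risk of both arms is disease progression while off drug. A safety endpoint confined to treated patients, with serious events reported as drug toxicity, cannot set that risk in one arm against the other.

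If the plan is followed as written, the trial could report HAART toxicity in full and still present no comparison of deaths or AIDS-defining events between the randomised groups, although it holds the data. The DSMB might also receive these events without a clear split by arm.

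**Working it through.** The plan gives no figure on this point, so there is none to reproduce. The check is a reading of the sections against each other, followed by an illustration of how many patients could be involved.

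**Step 1. Where would each event be counted?**

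*An untreated-arm patient has an AIDS-defining illness with CD4 at or above 350.*
- Recorded on the case report form (6.2.4): yes.
- Safety endpoint (9.2.2): no; the patient is not treated.
- DSMB and SAE tables (9.5, 9.6): possibly. Appendix III makes any clinical event judged serious or life-threatening grade 4. The heading is HAART toxicity, so coverage of untreated patients is unclear.
- Need for HAART (3.0): yes, if HAART follows. Section 6.1.4 and the Appendix II notes recognise starts for clinical as well as immunologic reasons. Section 9.6 gives this endpoint no analysis.
- Time to CD4 <350 (9.0): the illness is not an event. The patient stays at risk, and a later CD4 <350 still counts, though HAART may mean it never occurs.

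*A TL-HAART patient has the same illness after the planned stop.*
- Within the group named by the safety endpoint, but the illness is not drug toxicity. A single SAE percentage would not separate it from toxicity.
- The only SAE time window stated (6.3) is 8 weeks after the last dose. Planned follow-up after the stop is 36 − 12 = 24 months, and 8 weeks is 8/52 × 12 = 1.8 months, so about 22 months lie beyond it. Section 11.4 sets no end date, so later SAEs are not excluded; the coverage is simply not spelled out.

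*A patient in either arm dies before CD4 <350.*
- Recorded on the case report form: yes.
- Need for HAART: a death is not a start of HAART.
- Time to CD4 <350: the death is not an event, and how it is handled is not stated.

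In none of the three cases is there a named comparison of the event by randomised arm.

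**Step 2. How many patients might be involved?**

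The documents give no rate. Take an assumed 36-month risk r of death or AIDS before CD4 <350, for illustration only, with complete follow-up of the 180 planned subjects.

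Expected patients = 180 × r. Chance of at least one = 1 − (1 − r)^180.

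| Assumed r | Expected of 180 | Chance of at least one |
| --- | --- | --- |
| 0.5% | 0.9 | 59% |
| 1% | 1.8 | 84% |
| 2% | 3.6 | 97% |
| 5% | 9.0 | >99% |

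One patient is 1/90 = 1.1% of an arm. Even at the lowest assumed risk, at least one such event is more likely than not. At any of these risks the count is too small for a precise comparison.

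**The case against.** The best case against is that the plan already covers most of this. The DSMB meets every six months and sees SAEs and grade 3-4 events. Appendix III makes serious clinical events grade 4. Section 9.6 tabulates SAEs, section 9.0 has a catch-all with comparisons between groups, and section 3.0 compares the need for HAART in both arms. The time-to-event outcome is labelled immunologic, so a CD4-only definition fits its name. Neither the hypothesis nor the objectives promise a comparison of clinical progression.

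Much of this stands, and it rules out several stronger readings that a reader might infer:

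- *That these events reach no analysis and no DSMB item.* Not supported: many would arrive as SAEs or grade 4 events.
- *That a patient who dies or develops AIDS is censored as progression-free.* The protocol states no censoring rule, and an analysis plan may set one. For death, censoring is the usual default under a CD4-only definition. For AIDS it is wrong, because a living patient stays at risk.
- *That the trial can only measure harm from HAART.* CD4 count, viral load, time to CD4 <350 and need for HAART all bear on harm from withholding or stopping it.
- *That 3 to 16 events would be missed.* That range comes from 180 × 3 = 540 person-years at an assumed 0.5 to 3 per 100. It includes events after CD4 <350, which that analysis does not miss, and it assumes full follow-up.

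What the objection does not remove is the absence of a named comparison by arm. The SAE items are framed as HAART toxicity and the safety endpoint leaves out untreated patients. The catch-all names drug toxicity and treatment discontinuation and promises comparisons only where indicated. Need for HAART does not count deaths.

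**Conclusion.** The point holds in a limited form. Deaths, AIDS-defining events and other HIV-related events are collected in both arms, but no endpoint, analysis or monitoring item names them by randomised arm. An analysis plan could settle how death is handled in the CD4 <350 analysis. However, the endpoint list, the treated-only safety endpoint and the framing of the DSMB items are fixed in the protocol, and they point away from disease events.

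No size of bias is claimed, because no event rate is given; the 1 to 9 patients of 180 rest wholly on assumed risks. No effect on the 24-month viral load result is shown. The case for change is complete safety reporting of a strategy trial, using data already collected.

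**What to change.** 1. **Sections 9.2.2 and 9.6.** Add an intent-to-treat table by randomised arm, months 0-36, of deaths, AIDS-defining events, other HIV-related events and SAEs, with the difference between arms and its 95% confidence interval. Keep HAART toxicity in treated patients as a separate item.
2. **Section 9.5.** Give the DSMB the same listing by arm at each six-monthly review, outside the HAART toxicity heading.
3. **Section 9.0.** Keep time to CD4 <350 as immunologic progression. Add a supportive analysis of time to the first of CD4 <350, AIDS-defining event or death, so that in this analysis a death or AIDS event before CD4 <350 does not count as progression-free.

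The cost is protocol wording, one table, one listing and one supportive analysis; no new data collection is needed. The drawbacks are few events with wide intervals, and a composite that counts deaths unrelated to HIV, which is why it should be supportive and not replace the CD4 outcome.

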6.2.5 Adherence Questionnaires

The completion of the AIEDRP questionnaire (Appendix IV) will require an additional 5 minutes of time by the participant*.*

6.2.6 Laboratory Evaluations

Any laboratory toxicities that lead to a change in treatment, regardless of grade, must be recorded on the case report forms. At baseline, record all laboratory values. For post-baseline assessments, all laboratory values must be documented in the subject’s record but only grade 4 laboratory toxicities are to be recorded in the case report forms. Toxicities will be assessed using the Division of AIDS Table for Grading Adult Adverse Experiences,(Appendix III)

Hematology (CBC)

Hemoglobin, hematocrit, red blood cells (RBC), white blood cell count (WBC), differential WBC, absolute neutrophil count (ANC), platelets.

Chemistry Panel

Total bilirubin, AST (SGOT), ALT (SGPT), alkaline phosphatase, creatinine, indirect bilirubin, creatinine.

Lipid Panel

Total cholesterol, HDL and LDL fractionation, fasting triglycerides.

Pregnancy Test

For women with reproductive potential: Serum β-HCG or Urine test withsensitivity of 25-50 mIU/mL).

CD4 + Cell Count

Obtain absolute CD4+ cell counts and percentages at screening and at specified study visits. All laboratories performing these tests must possess a CLIA certification or equivalent. In order to perform CD4+ cell count testing that is used for patient management the laboratory also must participate in and be certified for protocol testing by the DAIDS Immunology Quality Assurance (IQA) Program, or its Canadian equivalent.

Evaluations for CD4+ cell counts should be performed at the same certified laboratory, if possible, for baseline calculation and throughout the course of the study. Because of the diurnal variation in CD4+ cell counts, determinations for individual subjects should be obtained consistently in either the morning or the afternoon throughout the study, if possible.

Note: Each time a CD4+ cell measurement is obtained, the local laboratory must perform a WBC and differential from a sample obtained at the same time.

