### 9.6 Analyses

Primary Endpoint

 The 24 month log plasma viral load will be compared between allocated groups on an intent-to-treat basis using linear regression to adjust for baseline plasma viral load and CD4 lymphocyte count.  All patients who have at least one post baseline visit will be included in the analysis. Patients who withdraw from follow-up prior to 24 months will have their 24 month viral load estimated using regression techniques based on group and individual trajectories.  Secondary sensitivity analyses using other analytic strategies including last observation carried forward will be used to assess the robustness of the result.

 Secondary Endpoints

Between group comparison of log plasma viral load at 36 months, and CD4 lymphocyte count at 24 and 36 months will be conducted in the same way as the analysis of 24 month viral load.

Subgroup analyses comparing treatment groups on the CD4 lymphocyte count and plasma viral load outcomes at 24 and 36 months will be carried out similarly, focusing (a) on patients treated in the acute stage and (b) patients treated early.

 A further analysis for each of the endpoints will be done using baseline CD4 lymphocyte count and plasma viral load, stage of disease, the interaction of stage and treatment, and treatment as predictors of outcome in a linear regression analysis.  This additional analysis is being done to perform formal statistical assessment of whether there are treatment by stage interactions. (The presence of an effect in one subgroup, and the lack thereof in another does not necessarily imply that the difference between the result in the two strata is statistically significant).

The toxicity of HAART will be presented using descriptive statistics as follows:

(a) percentage of patients discontinuing therapy because of toxicity

(b) percentage of patients suffering a serious adverse event (SAE)

(c) percentage of patients suffering a grade 3 or 4 adverse reaction

 All adverse events, including minor adverse events will be classified using the ACTG template.

 Confidence intervals around the percentages will be calculated.

##

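### Grade 3 laboratory toxicities that do not change treatment stay off the CRF and the rule for signs and symptoms contradicts itself, so the planned grade 3-4 safety summaries would be undercounted

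*Protocol*

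**What the plan says.** On data capture:

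- Section 6.2.6 (laboratory): once baseline is past, "only grade 4 laboratory toxicities are to be recorded in the case report forms"; the full set of results is kept at the site in each patient's own file. The exception reads: "Any laboratory toxicities that lead to a change in treatment, regardless of grade, must be recorded on the case report forms".
- Section 6.2.4 (signs and symptoms): "only Grade 4 signs and symptoms must be recorded on the case report forms", with a parallel exception: "Any signs or symptoms that lead to a change in treatment, regardless of grade, must be recorded on the case report forms". The same paragraph ends with a different rule: "All signs, symptoms, HIV-related and AIDS-defining events, and deaths must be recorded on the case report forms within 48 hours".

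On planned use:

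- Section 9.5, which sets six-monthly DSMB review, lists for the assessment of HAART toxicity: "Evaluation of grade 3 and 4 Adverse Events".
- Section 9.6, toxicity item (c), is the "percentage of patients suffering a grade 3 or 4 adverse reaction", to be reported with a confidence interval. The section adds that adverse events of every kind, minor ones included, will be classified on the ACTG template.
- Section 1.3, item 4, makes safety and tolerability a secondary objective, and section 9.2.2 lists HAART toxicity in treated patients as a secondary endpoint.

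**The concern.** The analysis sections ask for grade 3 and 4 events, while the capture sections send mainly grade 4 events to the database. A later analysis plan can choose how to summarise events, but it cannot recover ones that were never collected.

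The loss is also selective. A grade 3 laboratory toxicity enters the CRF through the treatment-change exception, and section 7.0 sets no protocol criteria for substituting or stopping HAART; it leaves those decisions to clinical practice. Capture therefore follows each physician's threshold for changing drugs and may differ by site. Item (c) would partly repeat item (a), discontinuation for toxicity, instead of describing severe toxicity in its own right. A confidence interval around the percentage would express sampling error only and would not show the missing events.

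**Working it through.** The plan gives no figure to reproduce, so the check follows each kind of event from the site to the database and compares the result with what sections 9.5 and 9.6 need.

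**Inputs.** Capture rules: sections 6.2.4 and 6.2.6. SAE route: section 11.4. Data keyed by sites on the CRFs: sections 11.1 and 11.2. Grading: Appendix III, where for example ALT above 5.0 and up to 10.0 x ULN is grade 3 and above 10.0 x ULN is grade 4. Outputs: sections 9.5 and 9.6.

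| Event after baseline | On the CRF? | Needed for 9.5 and 9.6(c)? |
| --- | --- | --- |
| Grade 4 laboratory toxicity | Yes | Yes |
| Grade 3 laboratory toxicity, treatment changed | Yes, by the exception | Yes |
| Grade 3 laboratory toxicity, treatment not changed (e.g. ALT 8 x ULN) | No | Yes |
| Grade 4 sign or symptom | Yes | Yes |
| Grade 3 sign or symptom, treatment changed | Yes, by the exception | Yes |
| Grade 3 sign or symptom, treatment not changed | Not required by one sentence of 6.2.4, required by another | Yes |
| Serious event of any grade | Own SAE form (11.4), whatever the CRF rule | Yes, if grade 3 or 4 |

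**Step 1, laboratory.** The third row is the gap. Section 6.2.6 has no offsetting sentence like the one in 6.2.4. The missing grade cannot be derived later from stored values, because the rule leaves post-baseline values in the subject's record. The protocol describes no other route to the database for a non-serious grade 3 laboratory event.

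**Step 2, signs and symptoms.** The sixth row depends on which sentence of 6.2.4 a site follows. Non-capture is not established here, but uniform capture is not assured either.

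**Step 3, direction of the error.** Let U be the percentage of treated patients who have at least one grade 3 reaction, none of grade 4, and no grade 3 reaction that reached the study data. Then

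reported percentage = true percentage - U, with U at or above 0.

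The error can only be downward, for given true events.

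**Step 4, size.** U depends on how often grade 3 is a patient's worst grade and on how often such events change treatment. The protocol states neither, so no value of U follows from it.

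**Step 5, minor events.** Grade 1 and 2 laboratory toxicities without a treatment change are also off the CRF, so the plan in 9.6 to classify minor events is unsupported for laboratory findings and uncertain for symptoms.

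**The case against.** The strongest reply has four parts.

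- **The CRFs are not limited to grade 4.** They take any grade that changes treatment, the last sentence on signs and symptoms in 6.2.4 asks for all of them, and serious events have their own form. Appendix III also counts clinical events judged serious or life-threatening as grade 4. All of this stands. It narrows the gap to grade 3 laboratory toxicities without a treatment change, plus an unclear rule for symptoms.
- **The data exist.** Values and toxicities are in the subject's record, which site monitors review (11.3), so they could be abstracted. This stands too. The accurate statement is that the outputs cannot be produced completely from the CRFs; the protocol plans no such abstraction.
- **Section 6.2.6 may be read too literally.** The CD4 count falls under the same heading, and a literal grade 4 rule would keep a secondary endpoint off the CRF. The sentence may govern toxicity reporting only, and detailed CRF instructions come from the data management center (11.2) and are not shown. This is a fair caution. If those instructions already collect all post-baseline safety values, the laboratory gap closes in practice, but 6.2.6 would still say otherwise and should be corrected.
- **Untreated controls are beside the point.** A reader might infer that grade 3 events in controls would not appear at all, because they have no treatment to change. The documents do not support that. The endpoint in 9.2.2 concerns treated patients, 6.1.4 provides for treatment starting in patients not randomized to HAART, and the 48-hour sentence would bring in their symptoms.

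**Conclusion.** The inconsistency is real and limited. As written, 6.2.6 withholds from the CRF grade 3 laboratory toxicities that leave treatment unchanged, and 6.2.4 gives two incompatible rules for signs and symptoms. The percentage in 9.6(c) and the grade 3-4 review in 9.5 would be incomplete and biased downward, with capture of grade 3 laboratory events depending on whether the physician changed treatment.

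A reader might infer that the CRFs hold grade 4 events only and that the grade 3 or 4 summaries cannot be produced at all. The exceptions, the 48-hour sentence, the SAE form and the source records rule that out. Nor can a number of percentage points be attached to the undercount: any range would rest on assumed rates for which the protocol offers no anchor.

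The matter touches one of three descriptive toxicity percentages for a secondary endpoint, and one item of the safety review. Items (a) and (b) in 9.6 and the primary 24-month viral load comparison are unaffected. The conclusion assumes that sites follow the CRF rules as printed and that no other transfer of laboratory data exists.

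**What to change.** 1. In 6.2.4 and 6.2.6, require all grade 3 and 4 signs, symptoms and laboratory toxicities on the CRF, plus any grade that leads to a change in treatment.
2. Reconcile the two sentences in 6.2.4. The later one should not simply be deleted, because it also carries the 48-hour CRF requirement for HIV-related and AIDS-defining events and deaths, which should stay.
3. Align the minor-events sentence in 9.6 with what is captured.

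Restricting 9.5 and 9.6(c) to the events now captured would also remove the contradiction, but it would give up the information on severe toxicity that these sections set out to provide.

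The change concerns data capture only and alters no clinical rule. The tests are already done and the results already documented at the sites, so the cost is some extra data entry. Left until after data collection, the same information would need chart abstraction across sites in two countries, for up to 180 patients followed for three years.

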4.1.2 No prior antiretroviral therapy (other than post-exposure prophylaxis)

4.1.3 For subjects who have been infected with HIV-1 for more than six months at study entry: HIV-1 RNA > 5,000 copies/mL obtained within 30 days of initiation of therapy performed by any laboratory that has a CLIA certification or its equivalent.

4.1.4 Laboratory values obtained within 30 days of initiation of therapy:

- Absolute neutrophil count (ANC) ≥ 750/mm^3^.
- Hemoglobin ≥ 7.0 g/dL.
- Platelet count ≥ 50,000/mm^3^.
- Creatinine ≤ 3 x upper limit of normal (ULN).
- AST (SGOT), ALT (SGPT), and alkaline phosphatase ≤ 5 × ULN.
- Total bilirubin ≤ 2.5 x ULN.

4.1.6 Negative serum pregnancy test at screening and negative urine or serum pregnancy test at the time of initiation of therapy in women of childbearing potential.

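### Post-baseline grade 3 laboratory toxicities that do not change treatment stay off the CRF (6.2.6), yet 9.5 and 9.6(c) count grade 3 and 4 events

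*Protocol*

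**What the plan says.** **What is collected.** Section 6.2.6 has all laboratory values recorded at baseline. After baseline, values are kept in the subject's record, but "only grade 4 laboratory toxicities are to be recorded in the case report forms". There is one exception: "Any laboratory toxicities that lead to a change in treatment, regardless of grade, must be recorded on the case report forms". Grading follows Appendix III, which has separate grade 3 and grade 4 bands for each of the tests discussed below.

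**What is to be analysed.** Section 9.5 lists, under HAART toxicity, "Evaluation of grade 3 and 4 Adverse Events", with review every six months. Section 9.6(c) reports the "percentage of patients suffering a grade 3 or 4 adverse reaction" and adds: "Confidence intervals around the percentages will be calculated". It also says that all adverse events, minor ones included, will be classified. Toxicity of HAART in treated patients is a secondary endpoint (9.2.2), and safety and tolerability is the fourth secondary objective (1.3). Section 9.0 plans descriptive statistics for drug toxicity, "with appropriate comparisons between groups as indicated".

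**Signs and symptoms.** Section 6.2.4 first limits mandatory CRF entry of signs and symptoms to grade 4. It then says: "All signs, symptoms, HIV-related and AIDS-defining events, and deaths must be recorded on the case report forms within 48 hours". Laboratory results are not in that list.

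**The concern.** The analysis asks for grade 3 and 4 events, while the collection rule delivers grade 4 plus whatever changed treatment. A later analysis plan cannot close that gap, because it can only work on what was entered.

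The gap can readily open in practice. Section 7.0 sets no protocol-mandated criteria for substituting or stopping HAART, so a grade 3 laboratory value need not lead to any change. At stake are the laboratory part of a stated secondary safety endpoint and the safety data put before the DSMB. An undercount of this kind is systematic, so the planned confidence intervals do not allow for it.

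**Working it through.** The protocol states no figure to reproduce. The check sets the collection rule against the analysis and then asks whether another section supplies the missing data.

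**1. Which post-baseline laboratory results reach the CRF under 6.2.6?**

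| Result | Changes treatment | Does not change treatment |
|---|---|---|
| Grade 4 | recorded | recorded |
| Grade 3 | recorded | **not recorded** |
| Grade 1-2 | recorded | not recorded |

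Sections 9.5 and 9.6(c) need both cells of the first two rows. The bold cell is missing.

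**2. Does another section restore it?**
- The 48-hour sentence in 6.2.4 omits laboratory results.
- Section 7.0 says that drug-associated toxicities are documented, but not where. Under 6.2.6 the subject's record would satisfy that.
- Section 11.4 covers SAEs only.
- The 9.6 sentence on classifying all adverse events states an analysis intention, not a CRF instruction.

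**3. Are these only abnormalities present at entry?** Not on the tests that have entry limits. The limits in 4.1.4 sit at the grade 2/3 boundary of Appendix III:

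| Test | Entry limit | Grade 3 band |
|---|---|---|
| Haemoglobin (g/dL) | ≥ 7.0 | 6.5-6.9 |
| ANC (/mm³) | ≥ 750 | 500-749 |
| Platelets (/mm³) | ≥ 50,000 | 20,000-49,999 |
| Creatinine (x ULN) | ≤ 3 | >3-6 |
| AST, ALT, alkaline phosphatase (x ULN) | ≤ 5 | >5-10 |
| Bilirubin (x ULN) | ≤ 2.5 | >2.5-5 |

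A grade 3 result on any of these is worse than the value that qualified the patient.

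**4. How many results fall under the rule?** Appendix II schedules CBC and chemistry at weeks 1 and 2 and months 1 to 12, which is 2 + 12 = 14 draws in the treatment year. With 90 treated patients, 14 x 90 = 1,260 of each panel. This counts opportunities, not events.

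**5. Direction and possible size.** Let p be the true percentage of patients with a grade 3-4 event, and m the share of those patients whose only such event is an unrecorded grade 3 laboratory result. Then the recorded percentage is p x (1 - m), which cannot exceed p. The protocol gives neither p nor m. With assumed values and n = 90:

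| True p | m = 1/3 | m = 2/3 |
|---|---|---|
| 10% (9/90) | 6/90 = 6.7% | 3/90 = 3.3% |
| 20% (18/90) | 12/90 = 13.3% | 6/90 = 6.7% |
| 30% (27/90) | 18/90 = 20.0% | 9/90 = 10.0% |

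Exact (Clopper-Pearson) 95% intervals at an assumed true 20%:
- m = 1/3: 12/90, 7.1-22.1%, which includes 20%.
- m = 1/2: 9/90, 4.7-18.1%, which excludes 20%.

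Whether the interval misses the truth therefore depends on an unknown share.

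**6. Between groups.** Take g3T and g3U as the percentages of treated and untreated patients whose worst laboratory grade is 3, and c as the share of the treated ones whose event changes treatment. While controls are off HAART, their grade 3 results are not recorded, so

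recorded minus true difference = c x g3T - (g3T - g3U) = g3U - (1 - c) x g3T.

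With g3T = 15 and g3U = 5 (both assumed), c = 0.25 gives 5 - 11.25 = -6.25 points, and c = 0.75 gives 5 - 3.75 = +1.25 points. This shows only that the direction is not fixed; it is not an estimate.

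**The case against.** **The impact is limited.** Grade 4 results, treatment-changing toxicities and SAEs are all captured, so 9.6(a) and 9.6(b) are unaffected. Grade 3 values remain in source. The CRFs are not shown and may collect more than 6.2.6 asks. All of this stands. It makes the bias conditional on 6.2.6 being followed, and it keeps the point minor.

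**The plan appears to intend fuller capture.** Sections 7.0 and 9.6 point that way. Neither sends grade 3 laboratory results to the CRF, so they confirm the mismatch without resolving it.

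**The term in 9.6(c) is adverse reaction, not adverse event.** One could argue that this leaves out laboratory findings. But 6.2.6 itself calls them toxicities and grades them on the adverse-experience table, and 9.5 lists grade 3 and 4 events under HAART toxicity.

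**A reader might infer that the two arms are recorded under different rules throughout the trial.** The documents do not support that. Section 6.2.6 states one rule for everyone; only its treatment-change clause operates differently. Controls who start HAART (6.1.4; Appendix II, footnote 7) come under that clause from then on. Treated patients normally stop at month 12 (5.1), after which most of both arms are off drug. The asymmetry therefore lies mainly in year 1, and it bears on a comparison that 9.0 merely permits.

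**A reader might also infer that the reported interval would exclude the true rate.** That is not general: in the working it depends on whether one third or one half of the affected patients are missed.

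**Conclusion.** The mismatch holds as written. Section 6.2.6 withholds from the CRF a class of events that 9.5 and 9.6(c) set out to count, and no other section supplies them. If 6.2.6 is followed and the analysis is drawn from the CRF data, the laboratory part of 9.6(c) and of the DSMB review can only be understated.

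The size is unknown. The figures above rest on assumed rates and are no forecast. A between-group comparison of laboratory toxicity, if one is made, could be off in either direction, mainly for year 1.

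The documents do not show that the data would be lost, since they can be recovered from the subject's record at the sites, nor that any reported result is in fact biased. The primary endpoint is not involved. This is a data-collection inconsistency that is worth correcting because correction is cheap, and it ranks as a minor point.

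**What to change.** 1. Amend 6.2.6 so that every post-baseline grade 3 and grade 4 laboratory toxicity is recorded on the CRF in both arms, whether or not treatment changes. Keep the present rule that a lower-grade laboratory toxicity is recorded if it leads to a change in treatment.
2. For patients already enrolled, back-enter earlier grade 3 laboratory results from the subject's record.
3. In 6.2.4, remove the conflict between the grade 4 limit on signs and symptoms and the 48-hour sentence, so that grade 3 clinical events are also on the CRF. Without this, amending 6.2.6 alone does not guarantee that the data match 9.5 and 9.6(c).

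The cost is a little more data entry, plus the back-entry for patients already enrolled. No new draws, visits or analyses are needed.
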